### Control for Potential Confounding Factors

Prognostic baseline factors including age, sex, mechanism of injury, and associated injuries will be recorded at the time of enrollment in the study and will be controlled during the statistical analysis.

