### Randomization

Using blocked sample randomization generates the randomization list. The permuted block method of randomization for a block size of four was used. Complete and incomplete SCI patients each are allocated to the two groups, early (E) and late (L).

Randomization will be stratified by site. Separate blocked sequences will be allocated to each of 4 sites, therefore patients referred to a particular site will be randomized regardless of the treatment sequences of other sites.

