### Descriptive and Explorative Statistics

Continuous variables including improvement of summed ASIA motor scores, summed ASIA sensory scores (light touch and pin prick) and the FIM scale will be managed with descriptive statistics (mean, SD, minimum, median, and maximum) and will be compared between treatment groups using the T-test.

Noncontinuous data including the occurrence and frequency of medical complications will be analyzed by the X^2 ^technique and organized in tables to include sample size, absolute and relative frequency.

The sample size was conducted on the percent of patients demonstrating an "improvement" in percent summed motor score. It is a dichotomous variable. This is our main method of analysis, but we also record ASIA motor score as a continuous variable to improve the power of our analysis.

In addition to univariable statistics, data will be analyzed by multivariable regression analysis to allow for statistical adjustment for important prognostic (confounding) factors.

Logistic regression is used to estimate the odds ratios and 95% confidence intervals. To perform data analysis, the SPSS-15 software applications are used. A P-value of less than 0.05 is considered statistically significant.

Factors suspected to be unbalanced between the groups would be accounted for by analysis of covariance.

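### Motor-score gains are compared by an unadjusted T-test and suspected imbalance picks covariates, while site, completeness of injury and admission motor score are never named for adjustment

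*Protocol article*

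**What the plan says.** Control for Potential Confounding Factors: "Prognostic baseline factors including age, sex, mechanism of injury, and associated injuries will be recorded at the time of enrollment", and these "will be controlled during the statistical analysis".

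Descriptive and Explorative Statistics makes four statements that bear on adjustment:
- Improvement in motor and sensory scores and the FIM scale "will be compared between treatment groups using the T-test".
- The main outcome is improved versus not improved: "It is a dichotomous variable. This is our main method of analysis". Logistic regression supplies odds ratios.
- Beyond the univariable comparisons, "data will be analyzed by multivariable regression analysis to allow for statistical adjustment for important prognostic (confounding) factors". No further list is given.
- "Factors suspected to be unbalanced between the groups would be accounted for by analysis of covariance".

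Randomization: "Randomization will be stratified by site", with separate blocked sequences (block size four) at four sites. The same section says that complete and incomplete injuries are each allocated to both arms, without saying whether completeness is a formal stratum.

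Neurologic Evaluation assigns every patient an initial motor score. Secondary purposes compare 12-month motor improvement separately in complete and in incomplete injuries.

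**The concern.** Site is a design factor and completeness may be one. Completeness and admission score are also natural predictors of later motor score. None of the three is named for adjustment.

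The imbalance rule cannot be relied on to bring them in. Blocked randomisation keeps a stratification factor close to balanced, so site, and completeness if it is a stratum, would seldom look unbalanced. The rule would instead admit whatever happens to differ by chance, so the model would depend on the observed data.

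At stake are precision for the dichotomous and continuous outcomes, and a single adjusted estimate for each score that is fixed in advance.

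**Working it through.** **Inputs from the article.** 149 per arm; control rate 9% (from complete injuries only); early rate 33%; 5% error; 80% power.

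**Assumed, not in the article.** Half of patients incomplete; common odds ratio 2.0 within completeness groups; control rate in incomplete injury 40%, 60% or 80%.

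**1. The plan's own figure.** 33% versus 9% at 80% power and two-sided 5% needs 45 per arm (53 with continuity correction), not 149. That discrepancy is a separate matter, and 149 is used here as stated. Power at 149:
- null SE = √(2 × 0.21 × 0.79/149) = 0.0472
- alternative SE = √((0.33 × 0.67 + 0.09 × 0.91)/149) = 0.0451
- (0.24 − 1.96 × 0.0472)/0.0451 = 3.27, so power exceeds 99.9%.

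**2. One case in full: incomplete control rate 60%, arms balanced on completeness.**
- Early rates: complete, odds 0.0989 × 2 = 0.198, rate 0.165; incomplete, odds 1.5 × 2 = 3, rate 0.75.
- Overall: 0.345 late, 0.458 early, difference 0.1126.
- SE used by the crude test: √(2 × 0.401 × 0.599/149) = 0.0568.
- Actual SE under balance: √((0.0819 + 0.1379 + 0.24 + 0.1875)/298) = 0.0466.
- Crude power: Φ((0.1126 − 1.96 × 0.0568)/0.0466) ≈ 51%.
- Stratified SE: √((2 × 0.1276 × 0.8724 + 2 × 0.675 × 0.325)/298) = 0.0471. Power: Φ(0.1126/0.0471 − 1.96) ≈ 67%.
- Crude type I error: null variance used 2 × 0.345 × 0.655/149 = 0.00303; actual 2 × (0.0819 + 0.24)/298 = 0.00216; ratio 0.712. The effective cut-off is 1.96/√0.712 = 2.32, which gives 2.0%.

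**3. The range.** Simulation, 20,000 replicates, pooled two-proportion test versus Mantel-Haenszel over two completeness strata, odds ratio 2.0:

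| Incomplete control rate | Power, crude | Power, stratified | Crude type I error, balanced on completeness | Crude type I error, not balanced |
|---|---|---|---|---|
| 40% | 65% | 71% | 3.4–3.6% | 5.1% |
| 60% | 51–52% | 67% | 1.9–2.0% | 5.1% |
| 80% | 23–24% | 53–54% | about 0.7% | 5.4% |

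The gain is 71 − 65 = 6 points at one end and 53 − 23 = 30 at the other.

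**4. The plan's own effect.** (0.33/0.67)/(0.09/0.91) = 4.98. With that odds ratio in both groups and balance on completeness, crude versus stratified power is 100% versus 100% (rate 40%), 99.9% versus 100% (60%) and 98% versus 99.8% (80%). The largest loss is about 2 points. This bound needs the balance. At the 80% rate the early rates are 0.33 and 0.952, so overall 0.641 versus 0.445. Without balance the crude test has 0.196/√(2 × 0.543 × 0.457/149) = 3.40, and Φ(3.40 − 1.96) is about 92–93%.

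**5. Adding site.** Logistic regression, 3,000 runs, 298 patients, blocks of four within site and completeness, assumed site log-odds shifts of −0.4 to +0.4. Incomplete control rates 30%, 50%, 70%:
- odds ratio 2.0: power 67% → 71%, 59% → 70%, 39% → 63%
- odds ratio 2.5: power 88% → 91%, 86% → 92%, 67% → 84%.

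At a conditional odds ratio of 2.0 the unadjusted model averages about 1.9, 1.7 and 1.5. This is the usual gap between a conditional and a marginal odds ratio, not bias in the trial.

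**6. Motor score.** With equal variances at both times and correlation r, a change score has variance proportional to 2(1 − r) and analysis of covariance to 1 − r². The ratio is (1 + r)/2: 0.90 at r = 0.8 and 0.80 at r = 0.6, so variance is 10% to 20% lower. The values of r are assumed.

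The admission motor score was not included in any simulation.

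**The case against.** The strongest reply is that this is a condensed article. Its list is introduced as examples, it promises multivariable regression for important prognostic factors, and the exact covariates may sit in an analysis plan that is not shown. That stands against one tempting reading, that the plan excludes site, completeness and admission score. They are unnamed, not barred. It does not answer the T-test or the imbalance rule, which are affirmative statements that a later plan would have to reverse.

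Three further objections have force:
- The T-test is the univariable step and already works on gains, so baseline is subtracted. True, but subtraction is less efficient than adjustment (step 6), and the article does not say which of the univariable and multivariable results is decisive.
- The imbalance sentence names analysis of covariance, a method for continuous outcomes. A reader might infer that the main dichotomous effect could be estimated several ways under that sentence. The text does not go that far; the rule bears mainly on the motor, sensory and FIM scores.
- A reader might infer a serious power loss or an invalid test. At the design effect the loss is small (step 4). Where the crude type I error departs materially from 5%, it is below it, and only if completeness is balanced by design, which the Randomization section leaves unclear.

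Nor is completeness ignored: it has its own secondary comparisons. Replacing those by an interaction test is optional and forms no part of this point.

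**Conclusion.** The point holds as a fault in how the analysis is fixed, not as an exclusion of key covariates. The plan states an unadjusted comparison of gains and an imbalance-driven covariate rule, and it leaves the randomisation stratum and two baseline factors recorded at entry unnamed.

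The benefit of naming them is about 6 to 30 points of power under the assumed mix, odds ratio 2.0 and incomplete control rates of 40% to 80%. It is at most about 2 points at 33% versus 9% with arms balanced on completeness. The unadjusted test is conservative (roughly 0.7% to 3.4%) only if completeness is a formal stratum; otherwise its type I error is about 5%. Only the 9% and 33% rates and the 149 per arm come from the article. The objection to letting suspected imbalance choose covariates does not depend on any of these figures. The change is worth making because it costs almost nothing.

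**What to change.** 1. In Descriptive and Explorative Statistics, make the main analysis the logistic regression of improved versus not on arm, with site, completeness and admission motor score fixed in advance. The factors already listed may stay if they too are fixed. State that the odds ratio is conditional on these covariates.
2. Replace the T-test on motor gains by analysis of covariance of the 12-month motor score on arm, with admission score, completeness and site.
3. Delete the sentence on factors suspected to be unbalanced.
4. Name the three factors under Control for Potential Confounding Factors, and say under Randomization whether completeness is a formal stratum.

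Cost: wording only, settled before outcome data are seen. No new data, visits or patients are needed.

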### Treatment

Emergency medical personnel will implement standard spinal immobilization and resuscitation techniques. All patients will receive intravenous methylprednisolone (30 mg/kg IV bolus over 15 minutes followed 45 minutes later by a 5.4 mg/kg/hr intravenous infusion over 23 hours if they arrive within the first 3 hours of injury and for 47 hours if they arrive between 3 and 8 hours post injury. [4] GI prophylaxis with antacids, H2 blockers or Proton Pump inhibitors will be prescribed.

### Early and late surgically decompressed group

The patients will be divided into two groups: Early (less than 24 hours from trauma) and late (between 24 and 72 hours following SCI). Because surgical technique varies according to the location of injury in the spine and the nature of the injury, surgeons are not restricted in their surgical technique. Radiographic parameters are evaluated on admission and post-operative images are done to assess the adequacy of decompression. Imaging studies are reported as soon as possible after the decompressive procedure but within a maximum of 7 days post treatment to assess the adequacy of the treatment.

Rehabilitation regimes start from the first day of trauma in all of the patients. Complications are identified and presented.

### Data Collection and Statistical analysis

Neurologic follow-up examinations are performed at routine in-hospital and outpatient follow-up visits by surgeons in each center. In all cases, the most recent follow-up data available are analyzed. In cases of delayed death, the last documented neurologic examination is used.

The following data is to be registered: age, sex, level of injury, the cause of trauma, time interval between trauma and admission, time interval between admission and operation, transition from the acute care hospital to rehabilitation, overall hospital (acute and rehabilitation) length of stay [23], complications such as pneumonia and atelectasis, superficial and deep sensory and motor index score and urinary and anal sphincter status on admission to the acute hospital; preoperative, postoperative and most recent motor scores at follow-up (at least 12 month follow-up).

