### Ethics

RCTs raise a number of ethical issues specifically related to the timing in the study design. If a patient has a potential chance of improvement by an early surgical decompression, it is ethically unacceptable to limit his/her access to this treatment. In both "early" and "late" decompression groups, everything including facilities and managements will be exactly the same except the time of decompression.

At first glance, the "difference" in chance of improvement between "early" and "late" groups seems unethical per se. During a group discussion we came to an agreement that what makes this RCT ethically unacceptable is not the above mentioned "difference" but withholding patients who could potentially benefit from early treatment. As the benefit of the timing of surgery is unclear and the timing of surgery in developed countries may be delayed as long as 4 or 5 days, delayed surgical intervention of greater that 24 hours is not an ethical concern. In developed countries, only 24% of SCI patients have access to a hospital setting that may provide early decompression surgery within the first 24 hours of injury [30]. This proportion is much less in developing countries because of lack of fundamental resources. [27]. We decided to set up a rapid response surgical team consisting of the same personnel providing regular care to SCI patients. When a SCI patient is referred to the hospital, he/she will randomly gets assigned into either the "early" or "late" treatment group. In the case of the "late" group, we will not interfere with the regular medical care process during the first 24 hours. If a patient comes to the hospital and he/she gets an "early" code, then the rapid response team will be summoned and the patient will be prepared for early surgery. We will not let the patient wait due to financial reasons, waiting lists, etc. All other interventions for rescue, resuscitation, hemodynamic stabilization, transport, imaging study, and surgical preparation will be provided in a standard way according to the guidelines of the hospital. Surgical, paramedical and nursing teams will be the same for both groups. Patients of the "early" group will benefit from the routine care provided for all other patients before and after surgery.

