### Allocation Concealment

A batch of sealed, opaque sequentially number envelopes will be provided to the supervising attending at each site. Whenever a patient is referred to a hospital, his/her name will be printed on the envelope and then the envelope will be opened. The patient will then receive the treatment identified within the envelope. The principal investigator will supervise commitment to the randomization process by reviewing the names printed on the opened envelopes and insuring that the patient receives the recommended treatment.

Unbiased examiners who are not involved in the management of the patients will perform the examinations. Thus, the design of the study is single-blinded.

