#### Limitations

Four surgeons in four hospitals will participate in this study. This introduces the potential for bias in treatment selection. The neurological examination may be subject to inter and intra-observer variability as this is not performed by a single, independent observer. Interobserver and intraobserver reliability of the radiologic measurements will be assessed in our study [34].

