## Conclusion

In conclusion, this study is aimed to study the effectiveness and indications of early and late surgical decompression in the setting of traumatic thoracolumbar SCI in a randomized format by independent, trained and blinded examiners [35]. This study can be a major step forward solving one of the controversial issues in the management of traumatic SCI.

This study provides an opportunity for ethically acceptable RCTs in many health related fields which will result in a considerable addition to the medical science.

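### The protocol promises blinded examiners uninvolved in care but assigns follow-up neurological examinations to the centres' surgeons, leaving the primary outcome open to unblinded assessment

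*Protocol article*

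**What the plan says.** All references are to the protocol article.

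- **Allocation Concealment:** "Unbiased examiners who are not involved in the management of the patients will perform the examinations". The next sentence draws the blinding label from this alone: "Thus, the design of the study is single-blinded".
- **Abstract (Background) and Conclusion:** both describe the comparison as made "in a randomized format by independent, trained and blinded examiners".
- **Data Collection and Statistical analysis:** "Neurologic follow-up examinations are performed at routine in-hospital and outpatient follow-up visits by surgeons in each center". The same paragraph says that the latest available follow-up data are what is analysed, and that after a delayed death the last recorded neurological examination is used.
- **Limitations:** "Four surgeons in four hospitals will participate in this study". The section adds that the neurological examination may vary between and within observers because "this is not performed by a single, independent observer".
- **Ethics:** "Surgical, paramedical and nursing teams will be the same for both groups".
- **Descriptive and Explorative Statistics; Clinical Significance:** the main analysis is dichotomous. A patient counts as improved with a gain of 5 points in the summed ASIA motor score.

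**The concern.** The article gives two rules for who examines patients after surgery, and they do not fit together on their face. Under one, the examiner stands outside the patient's care. Under the other, the examiner is a surgeon at the treating centre, seeing the patient at a routine visit.

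The difference matters because the timing of surgery cannot be hidden from those who operate, so examiner blinding is the only blinding claimed. The outcome is built from manual muscle test grades and then cut at 5 points. For a patient near the cut, a small difference in grading changes the classification. If examiners know the timing and hold a view on early surgery, the error can run in one direction by arm. Randomisation, intention-to-treat analysis and covariate adjustment do not remove that kind of error, and an examination cannot be repeated blind afterwards.

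**Working it through.** **Step 1: the text side by side.**

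| Question | Allocation Concealment, Abstract, Conclusion | Data Collection and Statistical analysis |
|---|---|---|
| Who examines? | Independent, trained examiners outside patient management | Surgeons in each centre |
| Blind to timing? | Yes | Not stated |
| Are the data analysed? | Implied | Yes: the latest follow-up is used |

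The surgeons' examinations are not described as a parallel clinical record. The sentence that follows sends follow-up data to the analysis. Nothing in the article says that the examining surgeons differ from the operating ones, or that they are kept unaware of allocation.

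**Step 2: how likely is a treating examiner?** Four surgeons in four hospitals averages one per site. The same surgical teams serve both arms. The allocation envelopes are also held within the clinical team: "sequentially number envelopes will be provided to the supervising attending at each site". Together these make a treating, aware examiner plausible, but they do not prove it.

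**Step 3: illustration of size.** Inputs from Sample size: control rate 9%, hoped-for early rate 33%, 149 per group. The amount of misclassification is an assumption.

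On the article's own figure: the pooled two-proportion formula for 33% vs 9%, two-sided 5%, 80% power gives [1.960·√(2·0.21·0.79) + 0.842·√(0.33·0.67 + 0.09·0.91)]² / 0.24² ≈ 44.0, rounded up to 45 per group, not 149. That is a separate matter. Here 149 is used only as the planned group size.

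Two-sided pooled z-test: z = d / √(2·p̄·(1−p̄)/149), where d is the observed difference and p̄ the mean of the two rates.

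| Rates compared | d (points) | p̄ | Standard error | z | p |
|---|---|---|---|---|---|
| 9% vs 14% | 5 | 0.115 | 0.0370 | 1.35 | 0.18 |
| 9% vs 16.5% | 7.5 | 0.1275 | 0.0386 | 1.94 | 0.052 |
| 9% vs 16.6% | 7.6 | 0.128 | 0.0387 | 1.96 | 0.050 (just below) |
| 9% vs 19% | 10 | 0.140 | 0.0402 | 2.49 | 0.013 |
| 33% vs 43% | 10 | 0.380 | 0.0562 | 1.78 | 0.075 |

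The significance threshold at a 9% control rate is therefore about 7.6 points. It should not be confused with the roughly 11.5 points that 149 per group detects with 80% power (138 per group are needed for 12 points, 160 for 11).

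**Step 4: chance of a false positive.** Suppose there is no true effect, and a fraction f of early-arm non-improvers is scored as improved. The early rate becomes p + (1−p)·f. For p=0.09 and f=0.10 it is 0.09 + 0.91·0.10 = 0.181.

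| f | Rejection probability, base rate 9% | Rejection probability, base rate 33% |
|---|---|---|
| 2% | 8% | 6% |
| 5% | 24% | 9% |
| 10% | 63% | 23% |

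The nominal rate is 5%.

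**The case against.** The two rules could be made compatible. The data-collection section speaks of surgeons in each centre, not of the operating surgeon. A surgeon with no part in the patient's care, kept unaware of the timing, would satisfy both. Nor does the Limitations section say that each hospital has exactly one surgeon, or that surgeons examine their own patients. This stands as far as it goes. A reader might infer that the operating surgeon scores the outcome and that the primary endpoint is therefore unblinded. The article does not say that, and the text promising independent examiners is equally current.

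A reader might also take the Limitations remark about observers as an admission that examiners are not independent. Its subject is reliability across observers, and several independent blinded examiners would fit it equally well. It supports neither side.

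Finally, the misclassification fractions have no source in the article, and a modest grading difference on one muscle reclassifies only patients already near the 5-point cut. The article does not show how many there are. The figures are an illustration, and the contradiction does not depend on them.

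What the objection does not supply is any sentence that makes the examining surgeons independent or blind. Nor is this detail that an article leaves to a fuller document: the article states both rules.

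**Conclusion.** The point holds as an unresolved contradiction over who performs the outcome examinations. Three places promise independent, blinded examiners, while the operative data-collection rule names the centres' surgeons and feeds follow-up data to the main analysis. Blinding is not secured, so the primary outcome is open to unblinded assessment. That it would in fact be unblinded is likely under the staffing described, but not established.

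The bias cannot be estimated from the article. Under the assumptions shown, a spurious shift of about 7.6 points suffices for significance at a 9% base rate, and 10 points exceeds it clearly. The effect is smaller at higher base rates, which matters because the 9% comes from complete injuries and the trial also enrols incomplete ones. The conflict should be settled before outcome data are collected, because analysis cannot repair it.

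**What to change.** Amend Data Collection and Statistical analysis as follows.

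1. Every motor examination entering an efficacy analysis is done by the examiners described under Allocation Concealment, who are told neither the allocation nor the time of surgery. This covers the admission and preoperative baseline, the postoperative examination, 6 weeks, 6 months, 12 months, the most recent follow-up, and the last documented examination used after a delayed death.
2. Surgeons' routine examinations are kept for care and do not enter the outcome data.
3. Where a surgeon's examination is the only one available, for example before a delayed death, it is flagged as unblinded, and a sensitivity analysis is run without it.

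The cost is wording and visit scheduling for examiners the article already plans, with possibly a few missing blinded assessments. The article does not give their number or availability at the four sites, so the sponsor should confirm that they can cover outpatient visits. If this cannot be done, the single-blind and blinded-examiner statements in the Abstract, Allocation Concealment and Conclusion must be withdrawn.

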**Methods:**

In this prospective, randomized clinical trial, 328 selected spinal cord injury patients with traumatic thoracolumbar spinal cord injury are to be randomly assigned to: 1) early surgery (before 24 hours); or 2) late surgery (24–72 hours). A rapid response team and set up is prepared to assist the early treatment for the early decompressive group. Supportive care, i.e. pressure support, immobilization, will be provided on admission to the late decompression group. Patients will be followed for at least 12 months posttrauma.

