### Purposes

#### Primary purposes

To determine whether early or late surgical decompression is effective in neurological improvement in the setting of traumatic spinal cord injury from T1 to L1.

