#### Secondary purposes

-To compare the neurological improvement in summed ASIA motor scores 12 months following a complete SCI in each of the early and late group of decompression

-To compare the neurological improvement in summed ASIA motor scores 12 months following an incomplete SCI in the early and late group following decompression

-To assess fusion success in the early and late group following decompression

-To assess sagittal alignment at the fracture level in the early and late group following decompression

-To compare the duration of acute hospitalization in the early and late group following decompression

-To compare the overall length of acute hospital stay in the early and late following decompression

-To compare the overall length of chronic hospital stay for rehabilitation [22] in each of the early and late decompression

-To assess the incidence of mortality in the early and late group following decompression

- To determine the frequency of complications in the early and late group following decompression

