### Neurologic Evaluation

Motor and sensory examinations are performed at admission to the acute hospital, preoperatively, immediately after surgery, and 6 weeks, 6 months, 12 months, and at the most recent follow-up.

Outcome is measured by using the American Spinal Injury Association ASIA summed motor and sensory scores [29] and the NASCIS [4,5] system to score neurological status and motor and sensory function.

Patients are to be assigned an initial motor index score from 50 to 100 which includes manual muscle test scores of all key muscles, sensory examination of pin prick and touch, sacral and deep tendon reflexes, and muscle tone evaluation. Sensory level is recorded as the most caudal dermatomal level of bilateral intact sensation.

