### Clinical Significance

We will consider a result significant if there is a 5-point or greater improvement in the summed ASIA motor score beyond what would be expected analyzing recovery in the setting of spinal cord injury [31]. It means that anyone who demonstrates a 5 point improvement will be classified as "improved'. We intend to conduct logistic regression on those who improve using the ASIA scale.

Intention to treat analysis will be used.

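### The main outcome is read at each patient's latest examination, or the last one before death, although the stated motor-score comparisons are at 12 months

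*Protocol article*

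**What the plan says.** All references are to the Protocol article.

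- Data Collection and Statistical analysis gives the rule for the examination used: "In all cases, the most recent follow-up data available are analyzed". The next sentence deals with deaths: "In cases of delayed death, the last documented neurologic examination is used".
- Secondary purposes fixes a time: "To compare the neurological improvement in summed ASIA motor scores 12 months following a complete SCI", with a matching item for incomplete injury.
- Primary purposes gives no time: "To determine whether early or late surgical decompression is effective in neurological improvement".
- Clinical Significance defines the responder, also without a time: "anyone who demonstrates a 5 point improvement will be classified as" improved. Survival is not part of the definition.
- Neurologic Evaluation lists the follow-up examinations after the immediate postoperative one as "6 weeks, 6 months, 12 months, and at the most recent follow-up", so the 12-month visit and the latest visit are separate items.
- The abstract sets a minimum and no maximum: "Patients will be followed for at least 12 months posttrauma". The list of data to be registered repeats that minimum: "most recent motor scores at follow-up (at least 12 month follow-up".

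**The concern.** The section on data collection is the only place that says when the main dichotomous outcome is read, and it gives a different answer from the secondary purposes. For any patient whose 12-month and latest status differ, an analyst cannot follow both. A choice that affects the main result is therefore left open until the data are in.

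The rule also mixes observation times. Early loss or death puts a patient's reading at a visit when less recovery may have taken place, while others are read after 12 months. A patient who gained 5 points and later died enters the analysis as a success.

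Unequal loss or death is not far-fetched on the protocol's own account. Sample size plans for 10% loss. Background reports an earlier randomised trial in which 20 of 62 patients (32%) were lost. Background and Risk/Benefit Discussion record a worry that early surgery raises complications, although the latter also cites evidence to the contrary. Only the examiners are blinded, and the early arm receives an added service.

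**Working it through.** The plan attaches no figure to this rule, so there is none to reproduce. I check the text first and then the likely size.

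**Which examination is analysed**

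| Patient | Examination analysed under the rule |
|---|---|
| Retained survivor | 12 months or any later date, no upper limit |
| Lost before 12 months | Last one attended: immediately after surgery, 6 weeks or 6 months |
| Died before 12 months | Last one documented, over the same range |

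Under the secondary purposes all three would be compared at 12 months. A patient who crosses the 5-point line only after 12 months is improved under one text and not under the other. Sample size also adds 10% as if lost patients gave no outcome, while the analysis rule gives them an earlier one.

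**Inputs for size.** From Sample size: improved rates of 9% and 33%, 149 patients per group, 5% error. The document does not say whether the 5% is one- or two-sided; I take it as two-sided. I use 149 only as the arm size; whether it follows from its own inputs is a separate matter. The shares who die or are read early, and the halved chance of improvement at an early reading, are my assumptions.

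1. **Deaths counted as improved.** Share of an arm = (proportion who die) × (proportion of those who had gained 5 points).
   - Low: 0.03 × 0.09 = 0.0027, or 0.3 percentage points (0.4 of 149 patients).
   - High: 0.10 × 0.33 = 0.033, or 3.3 percentage points (4.9 of 149 patients).
   - This is the content of one arm. With equal mortality and equal response among the dead it cancels between arms.

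2. **Equal early reading in both arms.** If 10% of each arm are read early at half the chance, each rate is multiplied by 1 − 0.10 × 0.5 = 0.95. Then 33% becomes 31.35%, 9% becomes 8.55%, and the difference falls from 24 to 22.8 points. This dilutes a true effect but does not create one.

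3. **Unequal early reading, no true effect, 33% improved in both arms.** Observed rate = 0.33 × (1 − 0.5f), where f is the share read early.
   - f = 5%: 0.33 × 0.975 = 0.3218. f = 15%: 0.33 × 0.925 = 0.3053. Spurious difference = 0.0165, about 1.7 points.
   - Standard error = √[(0.3218 × 0.6782 + 0.3053 × 0.6947)/149] = 0.0537, so the shift is 0.0165/0.0537 = 0.307 standard errors.
   - Two-sided rejection rate = 1 − Φ(1.96 − 0.307) + Φ(−1.96 − 0.307) = 0.049 + 0.012 = 6.1%, against 5%.
   - At the more extreme 0% versus 20%, the rates are 33% and 29.7%, the difference is 3.3 points and the rejection rate is 9.4%.
   - With 9% improved instead of 33%, the two cases give 0.45 and 0.9 points, and rejection rates of 5.2% and 5.9%.

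**The case against.** Four arguments carry weight on the other side.

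**There is a 12-month floor.** The abstract and the registered-data list both say at least 12 months. A reader might infer that the analysis corresponds to no stated time at all, or that any patient may be read at 6 weeks. The documents do not support that: retained survivors are read at 12 months or later, and earlier readings concern only losses and deaths. The floor sets no ceiling, however, and does not cover those patients.

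**Long follow-up is not itself a bias.** Allocation is by permuted blocks of four within site, so the arms fill almost in step and have nearly the same potential follow-up. The article gives no accrual period, so nothing can be said about how long the longest follow-up would be. What stands is that the estimated quantity is blurred. Bias requires loss or death to differ by arm.

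**The direction is open.** It is tempting to say that the rule favours the arm with more deaths. Compared with counting deaths as not improved, carrying the last score forward does raise that arm's rate. But if recovery continues over time, a last score taken early understates what the same patients would have shown at 12 months, and so lowers it. The documents do not decide between these.

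**Status while alive is a legitimate target.** Mortality is a listed secondary outcome, so deaths are not hidden, and counting them as not improved is one defensible choice among several. This stands. It does not answer the conflict between the two time points.

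**Conclusion.** The point holds as a defect in how the main outcome is defined. The explicit analysis rule contradicts the 12-month comparisons, mixes observation times, and can class a patient who has died as improved. This is more than detail left to an analysis plan, because the article states the rule.

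The likely numerical effect is modest. Under the assumed inputs, 0.3 to 3.3 percentage points of one arm's improved rate could be dead patients. Early reading in 5% versus 15% of the arms produces a spurious difference of about 1.7 points and a false-positive rate of about 6%. Both are small beside the planned 24 points and would matter more if the true effect were smaller. The documents give no loss or mortality by arm and no rate of improvement at early visits, so these figures illustrate scale and do not predict bias. A reader should not infer that the trial's conclusion would be overturned, or that one arm is systematically favoured.

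**What to change.** Reconcile Secondary purposes with Data Collection and Statistical analysis:

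- Define the primary outcome as an improvement of 5 points or more at the scheduled 12-month examination, for all randomised patients, with a stated window wide enough for routine visits. Treat later examinations as supportive only.
- Do not use last-score-forward as the primary rule for deaths and early losses. State a primary rule for each, for example deaths before 12 months counted as not improved, and patients alive but unseen imputed from their earlier scheduled scores. Report last-score-forward as a sensitivity analysis.
- Add the 6-week, 6-month and 12-month motor scores to the list of data to be registered. Neurologic Evaluation already schedules these examinations, but the list names only admission, preoperative, postoperative and most recent scores.

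The cost is mostly wording, with some extra data entry and analysis; no visit or patient is added. The downsides are small: follow-up beyond 12 months leaves the primary analysis, and some late visits may fall outside the window and become missing. The time point and the handling of deaths and losses should be settled before outcome data are seen, since a later choice would be open to challenge.
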